#### Secondary outcomes

Secondary outcomes are a change in: (1) physical performance according to the SPPB, (2) handgrip strength, (3) fatigue according to specific items of the CES-D scale, (4) gait speed, (5) dual-task gait speed, (6) depressive symptoms, (8) FRAIL and SARC-F scores, and (7) quality of life.

We hypothesize that the intervention group could present at least a 1-point increase in the SPPB, better measurements of strength and gait speed, less referred fatigue and depressive symptoms, and better quality of life.

All the participants will be coded using numbers and the data will be stored electronically. After storage, data will be checked by a second researcher to ensure data quality*.* All participant information will be stored in areas with limited access. All records that contain names or other personal identifiers will be stored separately from study records identified by code number.

### Statistical analyses

First, sample calculation was based in a previously published results from a clinical trial of resistive physical intervention among frail older adults [31]. This study is similar to our design and outcomes. In this trial, outcomes involved inflammatory biomarkers. To date, VIVIFRAIL trials were done in inpatients and nursing home patients and without inflammatory biomarkers as outcome measurement. For a 30% reduction in IL-6 with 80% power and a 5% error, we would have 18 older adults in each group for 12 weeks. Assuming a drop out until 25% within this period, the groups should be composed of 22 elder adults each.

Statistical analyzes will be performed using the SPSS program (version 23.0; SPSS, Inc., USA) and R version 3.6.2. Initially, the Shapiro Wilk and Levene tests will be used to test the distribution and homogeneity of the data. Descriptive analysis will be performed and the means and standard deviation of the variables with normal distribution will be presented, and the median and maximum and minimum values ​​for the non-normal variables and 95% confidence intervals.

Analysis by intention to treat will be performed. A sensitivity analysis will be performed for missing data, through multiple imputation. To compare the variables between the groups, the Student t-test will be used or the Mann-Whitney test for non-parametric variables. To assess the difference between the moments of intervention, one-way analysis of variance (ANOVA-oneway) with repeated measures or the Friedman test for nonparametric variables will be used.

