**Methods/design:**

This is a randomized clinical trial in an outpatient geriatrics clinic including older adults ≥60 years. For each frailty state (frail, pre-frail and robust), forty-four volunteers will be randomly allocated to the control group (*n* = 22) and the intervention group (*n* = 22) for 12 weeks. In the control group, participants will have meetings of health education while those in the intervention group will be part of a multicomponent exercise program (VIVIFRAIL©) performed five times a week (two times supervised and 3 times of home-based exercises). The primary outcome is a change in the inflammatory profile (a reduction in inflammatory interleukins [IL-6, TNF- α, IL1beta, IL-17, IL-22, CXCL-8, and IL-27] or an increase in anti-inflammatory mediators [IL-10, IL1RA, IL-4]). Secondary outcomes are change in physical performance using the Short Physical Performance Battery, handgrip strength, fatigue, gait speed, dual-task gait speed, depressive symptoms, FRAIL-BR and SARC-F scores, and quality of life at the 12-week period of intervention and after 3 months of follow-up.

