### Randomization and blinding

Participants will be allocated to groups (intervention or control group) randomly in 1:1 rate. The randomization sequence will be generated by an independent professional using an online system (www.randomization.com) to allocate 22 participants from each frailty group (i.e. frail, pre-frail and robust) to the control group (*n* = 66) and in the intervention group (*n* = 66). The type of intervention that the participant will undergo during the study will be indicated on a sheet of paper inserted in opaque, sequentially numbered, sealed envelopes. These envelopes will be prepared by a researcher who is not involved in enrolling the participants, in assigning them to their groups or performing follow-up measurements and will be delivered after baseline measurement. Follow-up measurement at the end of intervention period and after 3 months will be performed by a researcher who will be unaware of group allocation.

The professionals responsible for the physical and blood assessments will be blind to participant’s group. It will not be possible to blind the allocation of groups from the professional responsible for the intervention since the VIVIFRAIL protocol change according to patients’ profile. It will not be possible to hide the intervention of the participants, who will know about the allocation in different groups at random. However, they will not be aware of which group they were allocated. Raters and data-analysts will keep blinded in relation to the intervention performed by the volunteer.

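### The dropout allowance is miscalculated: 22 per group keeps the required 18 evaluable only up to about 18% loss, not the stated 25%

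*Protocol article*

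**What the plan says.** The whole sample-size justification is in the first paragraph of Statistical analyses in the protocol article. The target is set as "For a 30% reduction in IL-6 with 80% power and a 5% error", and the resulting requirement is "we would have 18 older adults in each group for 12 weeks". The allowance for loss follows: "Assuming a drop out until 25% within this period, the groups should be composed of 22 elder adults each".

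Two other places carry the 22 forward. The Abstract (Methods/design) assigns 44 volunteers in each frailty state, 22 to each arm. Randomization and blinding describes the sequence as one "to allocate 22 participants from each frailty group (i.e. frail, pre-frail and robust) to the control group", with the same number in the intervention arm, so 66 per arm and 132 in all. Neither place gives a different dropout rate or any further allowance.

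**The concern.** An allowance for dropout exists so that the required number of evaluable participants is still there after the assumed loss. Here the required number (18), the assumed loss (up to 25%) and the enrolled number (22) are all stated, and they cannot all be true. A reader who takes the paragraph at face value will believe that 80% power survives a quarter of participants leaving within 12 weeks, and it does not.

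At stake is the accuracy of the trial's only sample-size statement. The groups are small, so one or two participants more or fewer per group move power by a noticeable amount.

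**Working it through.** **Inputs, all from the protocol article.** Evaluable per group 18, power 80%, error 5%, dropout up to 25%, enrolled per group 22 (Statistical analyses); 1:1 allocation and 22 per arm in each of three frailty states (Abstract; Randomization and blinding).

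**Reproducing the plan's 22.** Multiplying by one plus the dropout rate gives 18 × 1.25 = 22.5, which becomes 22 when cut down. This is the likely route, though the article does not show its formula. Even this rule gives 23 if rounded up.

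**Correct inflation.** Enrolled n = evaluable n / (1 − dropout) = 18 / 0.75 = 24 per group. That is 48 per frailty state and 6 × 24 = 144 in total, against the planned 44 and 6 × 22 = 132.

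**What 22 delivers.**
- Evaluable at 25% loss: 22 × 0.75 = 16.5 per group, or 44 × 0.75 = 33 per frailty state (for example 17 and 16).
- Largest loss that still leaves 18: (22 − 18)/22 = 4/22 = 18.2%.

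**Effect on power.** The 18 cannot be rebuilt, because the article gives a 30% reduction in IL-6 but no standard deviation. I therefore took 18 as stated and solved for the standardised difference d that gives 80% power in a two-sample t-test at 5%, then recomputed power with fewer completers. Two features of the calculation are not stated, so both were varied: one- or two-sided testing, and whether 18 gives exactly 80% or was rounded up from just over 17 (17.01 was used, the most favourable case).

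| Assumption | d | 16 per group | 16.5 per group | 17 per group |
|---|---|---|---|---|
| Two-sided, 18 exact | 0.961 | 74.9% | 76.3% | 77.6% |
| Two-sided, 18 rounded up | 0.991 | 77.4% | 78.7% | 80.0% |
| One-sided, 18 exact | 0.846 | 75.6% | 76.8% | 77.9% |
| One-sided, 18 rounded up | 0.871 | 77.7% | 78.9% | 80.0% |

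The 16.5 column is the 25% case. Sixteen per group is a loss of 6/22 = 27.3% and 17 per group a loss of 5/22 = 22.7%, so these columns bracket it. The two 80.0% entries are 79.98% before rounding; they combine the most favourable rounding with a loss below 25%. At 16.5 per group power is below 80% in every row.

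In the two-sided case with 18 exact, the difference detectable with 80% power rises from 0.96 to 1.01 standard deviations.

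**The case against.** The arithmetic itself has no good defence. Reading 25% as a ceiling does not help, because an allowance should cover its own ceiling. Multiple imputation is planned only as a sensitivity analysis and does not restore 12-week information that was never collected.

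The stronger argument concerns weight, and most of it stands. The shortfall is two participants per group. Nothing is lost while dropout stays at or below 18.2%, and at the full 25% the loss is about 1 to 5 percentage points of power. No analysis or decision rule changes.

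It can also be said that the article never names the primary comparison as one within a frailty state; it speaks only of comparing groups. If the arms were pooled over the three states, 66 × 0.75 = 49.5 per arm would remain, well above 18. But the article does not describe a pooled primary comparison, and its groups of 22 are defined within a frailty state. The within-state reading is the natural one, but it is an assumption and should be labelled as such.

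A reader might infer that the trial simply fails to deliver 80% power. The document does not support that: the shortfall arises only if dropout exceeds about 18%. Nor does it support quoting a single figure such as 75% or 76%, which is the low end of a range that depends on unstated inputs. A reader might also expect that adjusting for baseline cytokine levels would make up the loss. The article gives no correlation between baseline and 12-week values, and does not say whether the 18 already assumed change scores or adjustment, so that cannot be claimed.

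**Conclusion.** The concern holds in a conditional form. The stated group size does not follow from the stated requirement and dropout rate: 22 per group supports about 18% loss, and 25% loss would need 24. At the full 25%, power is about 75–79%.

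The first part rests on the article's own figures alone. The power range rests on four assumptions: each group is one arm within one frailty state; the comparison is a two-sample t-test; 18 per group is taken as giving 80% power, exactly or after rounding up; and completers number 16 to 17 per group. These affect the size of the loss, not the finding that 18 evaluable participants are not kept.

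It is one calculation applied to three equal frailty states, not three separate errors. Classification: wrong as written, minor in magnitude.

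**What to change.** Correct the sentence in Statistical analyses; no additional enrolment is needed. It should say that 22 per group keeps 18 evaluable, and hence the stated 80% power, for dropout up to about 18%, and that at 25% dropout (16 to 17 completers per group) power falls below 80%. If a figure is given, it should be the range of roughly 75–79% with its assumptions stated: test, sidedness, and how 18 was rounded. If the sponsor holds the original calculation, its standard deviation and sidedness would replace the range by a single value. The text should not claim that a baseline-adjusted analysis recovers the shortfall unless a correlation and a calculation support it.

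The cost is one sentence, and a stated dropout tolerance or power that is slightly less favourable. Enrolling 24 per group (144 in total, 12 more than planned) would also make the figures agree, but the correction does not require it.

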**Fig. 2 Fig2:**
[figure not shown]
Proposed exercises illustration of each program of the VIVIFRAIL© multicomponent exercise methodology. Modified from Izquierdo and colleagues (2017)

The intervention will be discontinued due to any condition or adverse event that does not allow the performance of exercises with security or if requested by any participant. If necessary, one medical team will be disposable to offer assistance at any moment.

The participants will be instructed to does not enroll in other physical activity intervention during the period of 12 weeks of intervention.

After initial assessment and categorization, the multicomponent program will be carried out for 12 weeks, totaling 60 sessions. Two weekly supervisioned sessions will be held (60 min) with an interval of 1 day between them. Participants will receive all materials (elastic bands, towel and bottles with water/sand) to perform the exercises and will be trained to perform exercises individually at home 3 days weekly in order to complete 5 days per week. Instructions will be adapted to the focused population and will be provided in Portuguese. Adherence to the intervention will be monitored using a frequency control spreadsheet before the start of each session. Participants will be instructed to report possible adverse events.

Participants may withdraw from the study for any reason at any time. The investigator also may withdraw participants from the study in order to protect their safety and/or if they are unwilling or unable to comply with required study procedures. To promote participant retention and complete follow-up, all the participants will receive written feedback regarding the assessments performed.

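### The analysis is labelled intention to treat, but the named main tests use observed values only, imputation is left to sensitivity, and non-compliers may be withdrawn with no statement that they are still assessed

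*Protocol article*

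**What the plan says.** Under Statistical analyses, the protocol article promises intention to treat and, in the next sentence, places missing data in a secondary role: "Analysis by intention to treat will be performed. A sensitivity analysis will be performed for missing data, through multiple imputation". The main tests follow. For the comparison of arms: "To compare the variables between the groups, the Student t-test will be used or the Mann-Whitney test for non-parametric variables". For change over time: "one-way analysis of variance (ANOVA-oneway) with repeated measures or the Friedman test for nonparametric variables will be used". No missing-data method is named for these tests.

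The same section sizes the trial at 18 per group, allows for loss of up to 25% over the 12 weeks, and sets 22 per group. Outcomes are measured at baseline, 12 weeks and 24 weeks (Measurements; Table 4).

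The section on the intervention group describes two separate events. One is stopping the exercise, for safety or at the participant's request. The other is leaving the study: besides voluntary withdrawal, "The investigator also may withdraw participants from the study in order to protect their safety and/or if they are unwilling or unable to comply" with the required procedures. It does not say whether people in either position are still assessed at 12 and 24 weeks. It does mention written feedback on assessments, given to all participants, as a retention measure.

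**The concern.** Intention to treat means comparing the arms as randomised, with everyone randomised accounted for. A t-test or Mann-Whitney test omits anyone without the value being compared. Classical repeated-measures ANOVA and the Friedman test omit anyone missing any of the three visits. With imputation assigned to sensitivity, the natural reading is that the main result rests on those who happen to have data.

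The withdrawal clause makes this matter more, because the investigator may remove a person after randomisation for not complying. The exercise arm is asked for 60 sessions in 12 weeks, five days a week. The control arm is asked to attend monthly meetings. One rule applied to such unequal demands can produce unequal and selective loss. If those lost differ from those who stay, the comparison of arms is no longer protected by randomisation.

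**Working it through.** **1. The plan's own figure.** Inputs from Statistical analyses: 18 per group required, loss up to 25%, 22 per group recruited.
- 18 × (1 + 0.25) = 22.5, which gives 22 when rounded down. This reproduces the stated figure.
- 18 / (1 − 0.25) = 24 is the number that would leave 18 after 25% loss. The stated 22 is two short of it.

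**2. Who remains at 12 weeks at the plan's own maximum loss.**
- Lost: 22 × 0.25 = 5.5 per group, so 5-6 people.
- Observed: 22 × 0.75 = 16.5 per group, so 16-17, below the 18 required.
- Whole trial: six groups of 22 make 132, and 132 × 0.75 = 99 are observed.

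**3. Which test needs which visits.**
- The between-group test at 12 weeks is available-case. It needs the 12-week value, and baseline if change is analysed. A missing 24-week visit removes nobody from it.
- Repeated-measures ANOVA and Friedman need all three visits. Assuming a further 10% to 25% loss between 12 and 24 weeks (the article gives no figure), 16.5 × 0.90 = 14.9 to 16.5 × 0.75 = 12.4 per group remain.

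**4. What unequal loss could do to the comparison of arms.** Let a share p of an arm be lost, and let those lost differ from those who stay by δ (in SD units) on the outcome. The observed mean then differs from the mean of everyone randomised by p × δ. With the same δ in both arms:

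bias in the difference = δ × (p₁ − p₀)

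Neither δ nor unequal loss appears in the article, so both are assumptions.
- Loss 25% against 10%, δ = 0.5: 0.5 × 0.15 = 0.075 SD.
- Loss 25% against 10%, δ = 1.0: 1.0 × 0.15 = 0.15 SD.
- Equal loss in both arms with the same δ: 0.

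The sign depends on which arm loses more and on whether those lost have the better or worse outcomes.

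**The case against.** The strongest reply is that nothing here is a flat contradiction. The article never uses the terms complete-case or completers, and pairing intention to treat with imputation as a sensitivity analysis is common. The text is also a condensed article, and details of missing-data handling may sit in a fuller document. This stands in part: that the main analysis uses observed values is inferred from the tests named. But the point does not rest on a missing detail. The article itself chooses the tests and itself gives imputation a sensitivity role.

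A reader might go further and infer that the main result is a completers' analysis, confined to people who tolerated the exercise. The documents do not support that. Stopping the exercise is described apart from leaving the study, so someone who stops but attends at 12 weeks can be analysed as randomised. The three-visit requirement does not touch the 12-week between-group test. The withdrawal clause is permissive, covers both arms, concerns study procedures in general ("if they are unwilling or unable to comply with required study procedures"), and does not say that data already collected are discarded. Retention measures exist: feedback for everyone, and telephone contact after missed control meetings.

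A reader might also infer a bias in favour of exercise, or express it as a share of a planned standardised effect. Neither is supported. The article applies one loss figure to all groups and gives no direction. It states a 30% IL-6 reduction without an SD, so any standardised effect has to be back-solved from the 18.

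**Conclusion.** The point holds as a mismatch between the label and the stated methods. The article promises intention to treat, names main tests that use observed values only, puts imputation in second place, and permits withdrawal for non-compliance without securing later assessments. At the plan's own upper limit, a quarter of those randomised would be absent from the 12-week comparison, and the groups would fall below the required size.

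Whether this biases the result, by how much and in which direction, cannot be known from the document. The 0.08-0.15 SD is an illustration that rests on assumed loss of 25% against 10% and an assumed dropout difference of 0.5-1.0 SD. That possibility is enough to warrant a change before analysis, since the remedy is cheap.

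**What to change.** 1. **Follow-up.** State that participants who stop the intervention or do not comply with it remain in the study and are assessed at 12 and 24 weeks unless they withdraw consent. The rule for discontinuing exercise on safety grounds is unchanged.
2. **Main analysis.** Analyse all randomised participants in the arm assigned. Use multiple imputation as the main analysis, or a likelihood-based longitudinal model that takes the baseline value as one of the responses. A mixed model restricted to people with at least one post-baseline value would not be enough, because anyone lost for good before week 12 would still be dropped.
3. **Sensitivity.** Keep the observed-case tests already named, in this role.

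Both main-analysis options assume that loss is explained by the data collected, so the first change matters most: it reduces the amount of missing data. The cost is one sentence on follow-up, a swap of roles between analyses that are largely planned already, some effort to retain non-compliers, and slightly more analysis work. The visits are already scheduled.

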## Methods/design

### Design and participants

The present study is a single-center parallel randomized controlled trial comparing a multicomponent physical activity (i.e. VIVIFRAIL©) to usual health promotion. Participants are older adults from the Geriatrics Outpatient Center of Jundiaí Medical School, State of São Paulo, southwester of Brazil. These patients usually come from primary care centers or access the geriatric outpatient care directly.

Volunteers who meet the inclusion criteria will be randomly allocated to the intervention or control groups by an independent person, who is blind to their clinical data or frailty status. The data for participants in both groups will be obtained at three different times: at the beginning of the study, at the end of the study and after 3 months after the end of the intervention. The study flowchart is illustrated in Fig. 1. This study protocol follows the standard protocol for clinical trials in accordance with the SPIRIT2013 statement and follows the CONSORT statement for clinical trial transparency [20, 21]. The study is registered on the Brazilian Registry of Clinical Trials (REBEC) platform under the license RBR-9n5jbw. The study was approved by the Research Ethics Committee of the Jundiaí Medical School. For any ancillary study that data collection/request is not covered in the original informed consent process for this main trial, another signed consent will be obtained from every participant.

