### Measurements

Outcome measures will be done at three moments: baseline, after 12 weeks (end of intervention), and 24 weeks.

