#### Primary outcomes

The primary outcome measure is a change in the inflammatory profile after a 12-week multicomponent physical exercise program (VIVIFRAIL©), whether a reduction in inflammatory mediators in serum (IL-6, TNF- α, IL1beta, IL-17, IL-22, and CXCL-8) or culture supernatants (IL-6, TNF- α, IFN-gamma and IL-17) or an increased production of anti-inflammatory mediators (IL1RA and, IL-27) in serum or IL-10 and IL-4 in culture supernatants. We hypothesize that the intervention would lead to an anti-inflammatory profile.

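### Neither planned test is named as primary, adjusts for baseline or tests arm by time: the between-arm test loses precision, and the time-only test cannot isolate an exercise effect

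*Protocol article*

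**What the plan says.** The Statistical analyses section names two inferential procedures.

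- Between arms: "To compare the variables between the groups, the Student t-test will be used or the Mann-Whitney test for non-parametric variables". No covariate is given, and the variable compared (follow-up value or change) is not specified.
- Over time: "To assess the difference between the moments of intervention, one-way analysis of variance (ANOVA-oneway) with repeated measures or the Friedman test". Its stated purpose is "To assess the difference between the moments of intervention". Being one-way, it has time as its only factor.

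Beforehand, "the Shapiro Wilk and Levene tests will be used to test the distribution and homogeneity of the data", and the choice between the parametric and the rank version depends on distribution. Analysis is by intention to treat, with multiple imputation as a sensitivity analysis.

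Elsewhere in the article, the Primary outcomes section says: "The primary outcome measure is a change in the inflammatory profile after a 12-week multicomponent physical exercise program". The Measurements section says: "Outcome measures will be done at three moments: baseline, after 12 weeks (end of intervention), and 24 weeks". Design and participants describes a "single-center parallel randomized controlled trial comparing a multicomponent physical activity". No baseline covariate, arm-by-time term or primary efficacy test is named anywhere.

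**The concern.** A parallel randomised trial should rest its conclusion on a contrast between arms. Here the outcome is a change, yet the only procedure expressly aimed at change over visits has no arm in it. If cytokine levels drift in both arms through assay batch, season or regression to the mean, a time-only test can be significant with no exercise effect at all. With no primary test named, nothing stops such a result from being read as efficacy.

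The comparison that does involve the arms is loosely fixed. It uses no baseline covariate although baseline is collected from everyone, and the two readings of it (follow-up values or changes) can differ a good deal in power. With 22 per arm in each frailty group before dropout, precision matters. If the rank version is chosen, the named tests also do not estimate the percentage reduction in IL-6 on which the trial was sized.

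**Working it through.** **Inputs from the protocol article.** 18 evaluable per group, 80% power, 5% error and a 30% reduction in IL-6; 25% dropout and 22 per group; three frailty groups, 66 per arm in total. No SD, scale, sidedness or baseline correlation is given, so these are assumptions below.

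**1. The plan's own figure.** The 18 per group cannot be reproduced without an SD, so it is solved backwards. For a two-sided 5% two-sample t-test with 18 per group and 80% power, the standardised effect is d = 0.961, which implies an SD of 30/0.961 = 31% of baseline. A one-sided test would give d = 0.85, and a paired within-arm test d = 0.70. I take 0.96 to be on the scale of 12-week values; the article does not say so.

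**2. Relative variance of the arm difference**, with baseline correlation r and equal variances:

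- 12-week values: 1
- change scores: 2(1 − r)
- ANCOVA: 1 − r²

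For r between 0 and 1, 1 − r² never exceeds either of the others.

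**3. Power.** With 22 × 0.75 = 16.5 completers, use 16 per arm (one frailty group). The effective d is 0.961 divided by the square root of the relative variance; two-sided t-test.

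| r | 12-week t-test | Change t-test | ANCOVA |
|---|---|---|---|
| 0.3 | d 0.96, 75% | d 0.81, 60% | d 1.01, 79% |
| 0.5 | d 0.96, 75% | d 0.96, 75% | d 1.11, 86% |
| 0.7 | d 0.96, 75% | d 1.24, 92% | d 1.35, 96% |

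If 0.96 SD is instead taken to be on the change scale, the change-score t-test has 75% power, and ANCOVA has 86% at r = 0.5 and 81% at r = 0.7.

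**4. The time-only test under no arm effect.** Simulation: 18 per arm, three visits, the same shift in both arms at 12 and 24 weeks, 4,000 runs per setting, one-way repeated-measures ANOVA run separately in each arm at 5%.

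| r | Common shift (SD) | Exercise arm significant | Exercise significant, control not |
|---|---|---|---|
| 0.5 | 0.25 | 16% | 13% |
| 0.5 | 0.50 | 54% | 25% |
| 0.5 | 0.75 | 90% | 9% |
| 0.7 | 0.25 | 26% | 20% |
| 0.7 | 0.50 | 79% | 17% |
| 0.7 | 0.75 | 99% | 2% |

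In the same runs the between-arm t-test, on 12-week values or on change, rejected in about 4% to 5%. With independent arms and within-arm power p, the discordant pattern has probability p(1 − p), which peaks at 25% when p = 50%. That is why the last column rises and then falls.

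**The case against.** A between-arm test is planned, under intention to treat, in a 1:1 randomised trial. It controls type I error without adjustment, and the simulation confirms this. That stands: missing baseline adjustment costs precision, not validity.

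A reader might infer that the plan ignores baseline altogether. The text does not support that as fact. The outcome is defined as a change, so the t-test may be meant for change scores, in which case baseline enters by subtraction and the arm difference in change is tested. The sound complaint is that the article does not say which.

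A reader might also infer that within-arm significance will decide efficacy. The article does not say this, nor that the time test is run in each arm separately. It gives that test its own purpose. Misreading is a risk left open because no primary test is named; it is not a declared rule.

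It might also be inferred that the test could switch from visit to visit or stratum to stratum. The article does not say at what level normality is checked.

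Finally, the power gain is not a fixed quantity. It is small at r = 0.3, and at r = 0.7 a change-score t-test already reaches 92%. It also applies within a frailty group. If the groups were pooled, about 66 × 0.75 = 49 per arm would complete, and unadjusted power at the same effect already exceeds 99%.

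**Conclusion.** The concern holds in a limited form, as something that should be fixed. The methods stated in the article leave the primary test unnamed, leave the compared variable ambiguous, and contain no baseline covariate or arm-by-time term. This is a weakness in what is stated, not a detail left to an unseen analysis plan.

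The size is conditional. The 2% to 25% range needs a real shift common to both arms and inference from separate within-arm tests. The rise from 75% to between 79% and 96% needs the back-solved 0.96 SD to be on the 12-week scale and correlations of 0.3 to 0.7, none of which the article gives. The direction does not depend on these figures: in large samples ANCOVA is at least as precise as either unadjusted comparison, and a test without arm cannot attribute a change to exercise.

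**What to change.** - Name one primary test: the between-arm difference at 12 weeks by ANCOVA of the log mediator level on arm and log baseline. A mixed model over 12 and 24 weeks with baseline and arm-by-visit terms is equivalent in purpose.
- Report the ratio of geometric means with its 95% CI, so that the 30% reduction is estimated directly.
- State whether the inference is within each frailty group or pooled. Run the model within each group in the first case; add frailty stratum as a covariate only in the second.
- Fix the log scale in advance instead of letting Shapiro-Wilk choose the test.
- Label repeated-measures ANOVA and Friedman tests over time as descriptive.

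The cost is a change of wording before unblinding. Baseline is already collected, and the two packages named in the article (SPSS and R) both fit these models. No extra participants or measurements are needed.
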